##### Knee injury and osteoarthritis outcome score (KOOS)

The KOOS assesses knee pain, symptoms, and level of disability during the last week [23]. It has five subscales: Pain; Symptoms; Function in ADLs; Sports and Recreation; and Quality of Life. Each subscale has a normalized score from 0 to 100, where 0 represents extreme symptoms and 100 represents no symptoms. The test is valid, reliable, and responsive to change for people with knee OA [24]. The minimal detectable change (MDC) is from 8 to 10 points [25]. A validated Arabic version of KOOS will be utilized for this study [26].

##### Knee flexor and extensor muscles strength

An isokinetic dynamometer (Biodex Model 4Pro, N.Y. 11,967, U.S.A) will be used to assess isometric knee flexion and extension strength of both sides [27]. The hip angle will be at 85° of hip flexion and the knee angle will be at 60° of knee flexion [28]. Both legs will be tested, and the trial order will be randomized. Patients will be instructed to exert as much effort as they could for five seconds during each test. We will explain the test procedure to the participants and provide 5 min warm-up cycling before the test. To avoid fatigue, 60-s rest time between trials will be provided. The testing session will be directed by the same investigator, who will verbally encourage each participant to perform their best. The peak torque obtained over the 3 repetitions will be recorded. Peak torque measurement is considered the most valid method to assess the muscle strength in individuals with knee OA [29].

#### Secondary outcome measures procedures

##### Five times sit to stand test (FTSST)

The FTSST is an indicator of postural control, lower limb muscle strength, and balance [30]. Participants will stand up from a 45-cm chair with their arms over their chest and sit down five times as fast as they can without contacting the chair back. Start a timer at "go" and stop it when the participant's buttocks touch the chair on the fifth repeat. Participants can practice one trial before data collection. The FTSST has an excellent test–retest reliability (ICC = 0.960) in individuals with OA [31], and construct validity in people with rheumatoid arthritis [30].

##### 3-meter backward walk test (3MBWT)

The 3MBWT’s field begins and ends with marked colored tape. The participant will stand with their heels at the level of the front edge of the tape. Participants will be instructed to walk backwards 3 m when the investigator says “go” and stop when the participant passes the end-line tape. The participant can look back during the test. The test will only be administered once, and the time spend in completing the test will be recorded using a stopwatch. The investigator will walk behind the participant for safety. Participants will be advised to walk as fast as possible to the end line.

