Lower body positive pressure (LBPP) treadmill uses air pressure chamber to unload body weight during walking or running [16]. Reducing compressive forces at knee joint by decreasing body weight while walking or running often recommended to patients with knee OA [17]. Using LBPP for walking exercise stimulated weight loss and reduced knee pain [17]. LBPP has been shown to decrease knee pain in individuals with knee OA [17]. Compared to regular treadmills [18] in forward walking exercise, potentially by reducing the compressive forces at the knee joint while walking. However, previous studies only investigate forwarding walking exercise in LBPP. The advantages of backward walking exercise using LBPP have not been investigated yet. Thus, this randomized controlled trial (RCT) aims to investigate the effects of backward walking exercise using LBPP compared to forward walking on knee pain and functions in individuals with mild to moderate knee OA. We hypothesized that backward walking exercise could provide additional benefits to knee symptoms and functions more than forward walking exercise using LBPP. A secondary aim is to examine the effects of backward training compared to forward training on mobility functions, balance, and self-reported health status in this population.

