##### Blinding

This study is a single-blinded investigation. The group assignment will be concealed from the evaluator.

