##### Intervention

After signing the informed consent form, participants will fill out an intake form about demographic data and clinical variables. Additionally, they will be evaluated on inclusion/exclusion criteria. Participants meeting the inclusion criteria will be recruited in the study and assessed on the primary and secondary outcome measures. For test order, participants will be randomly assigned to one of four groups. A counterbalanced approach will be used to manage the order effects of learning and fatigue associated with the administered tests.

Participants will be randomized on the first day of the intervention to either a EG or CG. All participants will receive manual therapy and therapeutic exercise (Table 1) as described previously [12]. LBPP (AlterG Anti-Gravity Treadmill, Fremont, CA, USA) will be used for both forward and backward walking exercise (Fig. 3). All participants will have three sessions a week for 6 weeks (18 sessions) for up to 1 h/session. For the CG, gait training will be trained on forward walking using LBPP. The EG will be trained on backward walking using LBPP. For both groups, progression of gait training time will be instructed to gradually increase up to 30 min over the 6 weeks period. The air pressure inside chamber will be set to achieve pain free or max pain relief. Treadmill speed will be continuously assessed and increased gradually depending on the patient’s capacity. All participants will have 5 min of warm-up and cool-down exercise including heel raise, and hamstring and gastrocnemius-soleus stretches. All interventions and activities will be formed with a supervision of licensed physical therapists. Physical therapists will be trained on delivering the intervention and reporting the needed data each session. Before beginning the study, the evaluator will receive training on data collection and measuring all outcome measures.

**Table 1 Tab1:** Protocol exercise for all groups

Exercise	Procedure	Frequency	Intensity	Progression
Isometric quadriceps exercise	Patients lay in a supine position. A rolled-up towel was put beneath the knee. They were instructed to maximally activate their thigh muscles in order to straighten their knee and hold the contraction for 5 s	3 days/week	1 set of 10 repetitions/twice a day	1st week: 1 set 2–3 weeks: 2 sets 3–6 weeks: 3 sets

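### The 3-meter backward walk test times the task that only the experimental arm trains, in a single trial, so a difference on it cannot by itself show better general mobility or balance

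*Protocol article*

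**What the plan says.** Under Intervention, the arms differ in walking direction. For the experimental group, "The EG will be trained on backward walking using LBPP". For the control group, "For the CG, gait training will be trained on forward walking using LBPP". The dose is common to both: "All participants will have three sessions a week for 6 weeks (18 sessions) for up to 1 h/session".

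The 3MBWT section describes a timed backward walk along a taped course, done as fast as possible: "Participants will be instructed to walk backwards 3 m when the investigator says" go. It then fixes the number of trials: "The test will only be administered once, and the time spend in completing the test will be recorded using a stopwatch". It neither offers nor forbids a practice trial.

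The Introduction gives the secondary aim as the effect of backward compared with forward training "on mobility functions, balance, and self-reported health status in this population". The Abstract lists the 3MBWT with nine other secondary outcomes and does not distinguish it from them. Statistical analysis gives every outcome the same treatment: an independent t-test or Mann–Whitney test between arms at baseline and post-intervention, and a paired test within arms, at p < 0.05.

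Blinding covers one role only: "The group assignment will be concealed from the evaluator". Intervention adds that test order is counterbalanced over four groups to deal with learning and fatigue. Nothing in the article mentions that one outcome is also one arm's training task.

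**The concern.** The secondary aim asks a general question: does training backward improve mobility and balance more than training forward? The 3MBWT answers a narrower one, because it times the movement that one arm rehearses three times a week and that the other arm, as far as the protocol shows, meets only at the assessments. If the experimental arm is faster at T1, the result fits a general gain, task-specific skill, or both, and this test alone cannot separate them.

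What is at stake is the reading of a secondary outcome. With no interpretation rule fixed in advance, a significant 3MBWT result could be reported as a mobility or balance benefit when it partly shows that people get better at what they practise. The article gives the reader no warning against this.

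**Working it through.** The plan states no figure on this point, so the check sets the sections side by side and then illustrates how much could turn on it.

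**1. Trained task against tested task.** Intervention: experimental arm backward, control arm forward, both on the lower body positive pressure treadmill, 18 sessions. 3MBWT section: fast backward walking. Direction of travel, the feature that separates the arms, is also the feature that defines this test.

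**2. How each physical secondary test handles first exposure.**

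| Test | Practice described | Trials used |
|---|---|---|
| FTSST | yes ("Participants can practice one trial before data collection") | not stated |
| 3MBWT | none described | one |
| TUG | yes | one recorded, after earlier trials |
| FSST | none described | best of two |
| FRT | yes | mean of two |
| 10-MWT | none described | mean of two at each speed |
| 6MWT | none described | no repeat described |

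The 3MBWT shares the bottom position with the 6MWT. The difference is that forward walking is everyday activity for both arms, whereas nothing in the protocol gives controls practice at walking backward.

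**3. What the existing safeguards cover.** Counterbalancing balances order effects among tests within an assessment. It does not act on six weeks of one-sided training between T0 and T1. Evaluator blinding protects against biased scoring, not against a real difference in skill. A baseline comparison at T0 precedes the training and cannot show the asymmetry.

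**4. Illustration of size.** Inputs: n = 13 per arm (Allocation sequence generation) or 11 per arm (the number required before attrition, Sample size calculation); α = 0.05, taken as two-sided because sidedness is not stated; independent t-test (Statistical analysis). Assumption: training shifts the 3MBWT by d standard deviations through familiarity alone, with no general gain. The documents give no value for d.

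The test statistic has df = 2n − 2 and noncentrality d × √(n/2):
- n = 13: df = 24, √(13/2) = 2.550; d = 0.5 gives 1.275 and d = 0.8 gives 2.040.
- n = 11: df = 20, √(11/2) = 2.345; d = 0.5 gives 1.173 and d = 0.8 gives 1.876.

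Probability of a significant between-arm difference:

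| Assumed d | 13 per arm | 11 per arm |
|---|---|---|
| 0 | 5.0% | 5.0% |
| 0.2 | 7.8% | 7.3% |
| 0.5 | 23% | 20% |
| 0.8 | 50% | 43% |
| 1.0 | 69% | 61% |
| 1.2 | 84% | 76% |

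A small familiarity shift would rarely produce a significant result; a large one often would.

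**5. What a second trial does.** If trial errors within a visit are independent with variance v, one trial carries v and the mean of two carries v/2. The gain is in precision and applies to both arms. A practice trial reduces first-exposure effects, but one trial cannot stand in for 18 training sessions.

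**The case against.** The strongest reply is that better backward walking is a genuine effect of the randomised treatment. The arms are randomised, the same single trial applies to both, and the comparison is unbiased for what it measures. This stands. The limit is on generalising from the result, not on its validity.

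A reader might go further and infer that the test is bound to favour the experimental arm. The documents do not show this. Training takes place on a treadmill with body weight unloaded, the test is on a taped floor course, and how far one carries over to the other is not quantified. A gain in that direction is the reasonable expectation, no more. Multiplying 18 sessions by 30 minutes does not settle it either: walking time builds up to 30 minutes over the six weeks, so that product is not the planned exposure, and minutes do not measure an effect.

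A reader might also infer that the 3MBWT has no place under the mobility and balance aim. That does not follow. It is one of ten secondary outcomes, six other physical tests serve the same aim, and the article nowhere says that the conclusion will rest on this one.

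On blinding, a practised backward gait at T1 could be a cue to allocation, since the investigator walks behind the participant. This is plausible but not shown. The article gives neither the four test orders nor which tests they include, so it cannot be said which later assessments would be exposed.

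It may also be said that an article leaves interpretation to the full protocol. But the article does fix the single administration and does place the test undifferentiated among the mobility and balance outcomes. Those choices can be judged as written.

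**Conclusion.** The point holds as a limit on interpretation together with a cheap improvement to the measurement. A between-arm difference on the 3MBWT at T1 is expected to reflect task-specific learning at least partly, and cannot by itself support a conclusion of better general mobility or balance. The randomised comparison on the test remains valid. The primary outcomes (NPRS, KOOS and thigh muscle strength) are not affected by task familiarity.

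The size is unknown. Over assumed shifts of 0.2 to 1.2 standard deviations, the chance of a significant result with no general gain runs from about 8% to 84% with 13 per arm and from about 7% to 76% with 11. These figures rest on a two-sided 5% t-test and on assumed shifts that the documents neither give nor exclude. The qualitative conclusion needs only that one arm trains the tested movement and the other does not, which the article states.

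**What to change.** (a) State, before results are seen, that the 3MBWT is a trained-task outcome and that the mobility and balance conclusion rests on the FTSST, TUG, FSST, FRT, 10-MWT and 6MWT. Note there that the FSST includes backward steps and so is not wholly free of the trained movement. This is the change that answers the concern, and it costs a sentence.

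(b) In the 3MBWT section, replace the single administration with one practice trial followed by two recorded trials, analysed as their mean, at both T0 and T1. This improves precision and reduces first-exposure effects but does not remove the training asymmetry, so it supplements (a) and does not replace it. It costs a minute or two per visit.

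(c) Optionally, place the 3MBWT last at both T0 and T1, so that any cue to allocation comes after the other evaluator-scored tests. Moving it at T1 only would change the test conditions between visits and confound the planned pre–post comparison with order and fatigue. The cost is that the test leaves the counterbalancing and is always done when participants are most tired, equally in both arms and at both visits.

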##### Timed up and go test (TUG)

The TUG evaluates an individual’s functional mobility by asking them to stand up, walk toward a cone placed of 3 m from the chair at a normal speed, turnaround 180 degrees, walk back 3 m, and sit down [32]. The TUG has an excellent reliability and validity in people with knee OA [33]. The participants will be allowed to have one-practice trials. The third TUG trial will be recorded and documented.

##### Four square step test (FSST)

The FSST is designed to assess dynamic balance and coordination. Participants will step forwards, sideways, and backwards as fast as they could over 4 canes that shaped plus sign without touching the canes. Start in square 1 facing square 2. Participants will follow the following order: square number 2, 3, 4, 1, 4, 3, 2, and 1. Participants can use walking aid during the test. Two trails will be performed, and the best trial will be documented. The trial will be repeated if the participant unsuccessfully completed the sequence. The time will be recoded when the first foot makes contact with square 2 and stopped when the last foot makes contact with square 1. The test has an excellent reliability and validity in individuals with hip OA [34].

##### Functional reach test (FRT)

Participants' stability and balance are evaluated using the FRT by measuring how far they are able to lean forward from a standing position. Participants extend their arm with a closed fist and leaning forward as possible without taking a step. On the yardstick, the beginning position will be marked at the 3rd metacarpal proximal edge. The highest achievable distance will be marked as ending position. The distance between the beginning and ending positions will be computed. One-practice trials will be permitted. The participant will complete two trials. The analysis will utilize the average of the two trials. The FRT has high intra-rater reliability (ICC = 0.98) and validity (*r* = 0.71) [35].

##### 10-meter walk test (10-MWT)

The 10-MWT evaluates walking speed over a brief period of time with or without the use of an assistive device. The participant will walk 10 m with an acceleration and deceleration zones for first and last 2 m. Only the 6 m distance in between will be used for scoring. The 10-MWT has excellent test–retest reliability with different populations [36, 37]. The 10-MWT has MCID of 0.13 m/s for significant meaningful change in older adult [37]. Participants will perform the test twice at comfortable speed and twice at fast speed, and the average of the results speeds will be utilized for the analysis separately.

##### Six minute walk test (6MWT)

6MWT measures aerobic endurance through distance walking during 6 min. Participants may take as many time as desired for standing rest; however, the investigator must continue timing. The number of standing rests and the duration of each standing will be recorded. Assistive device or braces are allowed and will be documented.

#### Medical outcomes study short form 12 (SF-12)

This medical health survey evaluates health related QoL for research and clinical practice purposes. This measure is a shortened version of medical outcomes study short form 36 (SF-36). It measures eight different aspects of health and well-being. The total score ranges from 0 to 100, where 0 reflects the worst QoL and 100 reflects the best. The Arabic version of the SF-12 has been translated and validated [38].

##### Patient health questionnaire -9 (PHQ-9)

The PHQ-9 is a questionnaire for evaluating depression symptoms. It comprises nine items, each of which asks the participants to score the severity of their depression symptoms on a 4-point Likert scale over the last two weeks ranging from 0 “Not at all” to 3 “Nearly every day”. A total score of 5–9 indicates minimal depression symptoms, 10–14 indicates moderate symptoms, 15–19 indicates substantial symptoms, and score of 20 or higher indicates severe depression [39, 40]. This tool is reliability and validity in previous investigation [41]. This tool has been translated and validated into different languages including Arabic language [42].

##### Rapid assessment of physical activity (RAPA)

The RAPA is a subjective survey that consists of nine questions that examines the physical activity of elderly. The physical activity is classified into three categories (light, moderate, and vigorous) along with textual and graphical descriptions [43]. Arabic language of RAPA measure has been translated and validated [44].

### Procedure

#### Assignment of intervention

##### Allocation sequence generation

In a ratio of 1:1, the participants will be allocated randomly into an experimental group (EG, *n* = 13) or a control group (CG, *n* = 13), using an online randomization website (https://www.graphpad.com/quickcalcs/randomize1.cfm), a research assistant who is not involved in the intervention or data collection will generate the randomization.

##### Allocation concealment

The random assignment for each participant will be placed in an anonymous envelope. Envelopes will be prepared by an independent research assistant, who will then conceal information for the evaluator investigator. Following completing the baseline evaluation, the independent research assistant will draw an envelope and notify a trained physical therapist of group assignment for each participant.

##### Blinding

This study is a single-blinded investigation. The group assignment will be concealed from the evaluator.

##### Intervention

After signing the informed consent form, participants will fill out an intake form about demographic data and clinical variables. Additionally, they will be evaluated on inclusion/exclusion criteria. Participants meeting the inclusion criteria will be recruited in the study and assessed on the primary and secondary outcome measures. For test order, participants will be randomly assigned to one of four groups. A counterbalanced approach will be used to manage the order effects of learning and fatigue associated with the administered tests.

Participants will be randomized on the first day of the intervention to either a EG or CG. All participants will receive manual therapy and therapeutic exercise (Table 1) as described previously [12]. LBPP (AlterG Anti-Gravity Treadmill, Fremont, CA, USA) will be used for both forward and backward walking exercise (Fig. 3). All participants will have three sessions a week for 6 weeks (18 sessions) for up to 1 h/session. For the CG, gait training will be trained on forward walking using LBPP. The EG will be trained on backward walking using LBPP. For both groups, progression of gait training time will be instructed to gradually increase up to 30 min over the 6 weeks period. The air pressure inside chamber will be set to achieve pain free or max pain relief. Treadmill speed will be continuously assessed and increased gradually depending on the patient’s capacity. All participants will have 5 min of warm-up and cool-down exercise including heel raise, and hamstring and gastrocnemius-soleus stretches. All interventions and activities will be formed with a supervision of licensed physical therapists. Physical therapists will be trained on delivering the intervention and reporting the needed data each session. Before beginning the study, the evaluator will receive training on data collection and measuring all outcome measures.

**Table 1 Tab1:** Protocol exercise for all groups

Exercise	Procedure	Frequency	Intensity	Progression
Isometric quadriceps exercise	Patients lay in a supine position. A rolled-up towel was put beneath the knee. They were instructed to maximally activate their thigh muscles in order to straighten their knee and hold the contraction for 5 s	3 days/week	1 set of 10 repetitions/twice a day	1st week: 1 set 2–3 weeks: 2 sets 3–6 weeks: 3 sets
Straight leg raising (SLR) exercise	Patients lay in a supine position. They were instructed to perform a maximum isometric quadriceps contraction prior to the lifting phase of the exercise. Then they were instructed to lift the leg up to 10 cm above the plinth and hold the contraction during the lifting phase for 10 s	3 days/week	1 set of 10 repetitions/twice a day	1st week: 1 set 2–3 weeks: 2 sets 3–6 weeks: 3 sets
Isometric hip adduction exercise	Patients lay in a supine position. A small pillow was put between the knees. They were instructed to perform isometric hip adduction exercise while pressing the pillow between the knees and to maintain the adduction with contraction for 5 s	3 days/week	1 set of 10 repetitions/twice a day	1st week: 1 set 2–3 weeks: 2 sets 3–6 weeks: 3 sets
Terminal knee extension exercise	Patients lay in a supine position. The affected knee is flexed about 30 degrees over a rolled towel. The patients were instructed to extend the knee to zero degree and hold it for 5 s then gradually flex the knee to starting position	3 days/week	1 set of 10 repetitions/twice a day	1st week: 1 set 2–3 weeks: 2 sets 3–6 weeks: 3 sets
Semi-squat exercise	Patients were asked to stand against the wall and performed semi-squat to 45- degrees flexion at knees and held this position for 30 s	3 days/week	1 set of 10 repetitions/twice a day	1st week: 1 set 2–3 weeks: 2 sets 3–6 weeks: 3 sets
Leg press exercise	Patients were asked to perform leg press exercise on a standard leg press machine. Patients were asked to press the machine to extend the knee to zero degree and hold it for 5 s then gradually flex the knee to starting position	3 days/week	1 set of 10 repetitions/twice a day	1st week: 1 set 2–3 weeks: 2 sets 3–6 weeks: 3 sets

From Alghadir et al. [12] with permission

